| Control Intervention | The control group consists of the study population of the StOP?-study. In this population the wound closure was done by the operation team under supervision of the main surgeon. |
| Number of Participants with Rationale: | Total of participants: 1160 (580 trial group, 580 control group). |
| Study Duration: | 2x9 months |
| Study Schedule: | Month Year of First-Participant-In:1.3.2016  Month Year of Last-Participant-Out: 30.11.2017  (baseline = 2^nd^ arm from the STOP? trial 1.3.2016 – 30.11.2016;  Intervention: 1.3.2017 – 30.11.2017) |
| Investigator(s): | [name]. med. [name], Department of Visceral Surgery and Medicine, University hospital Bern (Inselspital), 3010 Bern |
| Study Centre(s): | University hospital Bern (Inselspital) |
| Statistical Considerations: | Sample size: The incidence of SSI after abdominal surgery in the department for Visceral Surgery and Medicine is 20%. The aim is to detect a reduction of the overall incidence rate of SSI from 20% to 14% after a follow-up of 30 days. We defined the level of significance at 5% and power of 80%, assuming normal approximation to binomial distribution requires 484 surgeries in each cell, thus 968 patients overall. In the ongoing StOP?-study we have a drop out and study refusal rate of maximal 20%. Thus, a total of 1160 participants (580 per arm) need to be included.  Duration: The average number of laparotomies from 8:00 AM to 5:30 PM from Monday to Friday per year are 720. The study schedule includes first 9 months in the control (baseline: 2^nd^ arm of the STOP? Study) and then 9 months in the intervention group.  Outcome parameters will be assessed the same way as in the ongoing StOP? Study. Thus, the results of the StOP? Study will be used as the control arm and the intervention arm will start after termination of the StOP? study. |

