# STUDY OUTCOMES

## Primary Outcome

SSI that occur after surgery will be assessed according to the criteria developed by the Centers for Disease Control and Prevention^14^. Infections will be categorized as incisional (superficial or deep) infections or organ–space infections. Superficial SSI (type 1) involve only skin and subcutaneous tissueand exclude stitch abscesses. Deep SSI (type 2) involve deeper soft tissues, like fascia and muscle, at the site of incision. Organ–space SSI (type 3) involve any organ or body cavity.

Incidence of SSI is assessed according to the clinical routine, following the established protocol of Swissnoso. Data collection according to the Swissnoso protocol will be extended to all surgeries included. The protocol includes direct contact to the patient:

- All patients receive a standardised follow-up phone call at least 30 days after the operation to assess incidence of SSIs and other complications.
- If patients do not respond to follow-up phone calls, five documented attempts to contact the patients followed by rapid contacts with the subject’s general practitioner or other medical staff involved in the medical treatment of the patients, will be performed before loss of follow-up is documented.

Surveillance according to Swissnoso is performed by the department of infectious diseases of the University hospital of Bern and are further supervised by external reviewers from Swissnoso. Therefore the observers are independent and evaluation bias is minimized.

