## Secondary Outcomes

The assessment of postoperative mortality will be included to the telephone interview and assessed as follows:

Mortality at 30 days: Observer receives the information during the follow-up phone call that the patient died. If patients do not respond to follow-up phone calls, five documented attempts to contact the patients followed by rapid contacts with the subject’s general practitioner or other medical staff involved in the medical treatment of the patients, will be performed before loss to follow-up is documented. In addition, the Zivilstandsamt will be contacted once 3 months after surgery.

Postoperative fascial dehiscence at 30 days postoperative.

Complications: Assessment according to Clavien-Dindo grading

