# STUDY DESIGN

## General study design and justification of design

Prospective controlled, two armed, observational, monocentric study (before and after study).

To evaluate the impact of a specialised wound-closing team on surgical site infections

Included in the study are all patients (over 18 years, elective and emergency) with laparotomy and closure of the wound from Monday to Friday from 8:00 to 17:30 o’clock. We aim to include a total of 1785 participants.

The control group consists of the study population of the StOP?-study. In this population the wound closure was done by the same operation team under supervision of the main surgeon.

The screening of the first participant in the control group started on the 01.03.2016 and ended with the STOP? study on the 30.11.2016. The inclusion of patients in the intervention group takes place between 1.3.2017 and 30.11.2017. Therefore the end of data collection will be the 31.12.2017.

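### The stated end of data collection (31.12.2017) falls before the protocol's own 3-month mortality registry contact for patients operated on in October and November 2017, and leaves almost no time for the day-30 contact procedure in the last patients

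*Protocol*

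**What the plan says.** Protocol section 6.1 (General study design) sets the accrual window: "The inclusion of patients in the intervention group takes place between 1.3.2017 and 30.11.2017". From this it infers the closing date: "Therefore the end of data collection will be the 31.12.2017". For the control group it says only that screening "ended with the STOP? study on the 30.11.2016".

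Section 5.1 (Primary Outcome), repeated in 9.1.1, sets the contact for SSI and complications: "All patients receive a standardised follow-up phone call at least 30 days after the operation to assess incidence of SSIs and other complications". This is a minimum with no upper limit. If the patient does not respond, the procedure is "five documented attempts to contact the patients followed by rapid contacts with the subject’s general practitioner" or other treating staff, and only then is the patient documented as lost to follow-up.

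Section 5.2 (Secondary Outcomes) uses the same steps for 30-day mortality and adds one more: "In addition, the Zivilstandsamt will be contacted once 3 months after surgery". Section 9.1.2 repeats this.

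The synopsis, under Study Schedule, gives "Month Year of Last-Participant-Out: 30.11.2017", which is also the last day of inclusion. Elsewhere the synopsis gives every patient 30 days of follow-up and says that outcomes are assessed as in the StOP? study.

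**The concern.** The protocol implies three different end dates: 30.11.2017 (synopsis), 31.12.2017 (section 6.1) and 28.02.2018 (last inclusion plus the 3-month registry contact). They cannot all be followed. Staff who stop on 31.12.2017 omit a planned check for the last two months of intervention patients. Staff who continue depart from the stated end date.

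This matters because the comparison is a non-randomised before-after study, which depends on finding events equally well in both periods. A patient who has died cannot answer the telephone, so the registry contact is the backstop for mortality in patients whom no other source reaches. Mortality is to be analysed by interrupted time series (section 10.4.2), and the affected operations sit at the end of the intervention series. With about 36 post-intervention points (section 10.4.1), 22% is roughly the last 8.

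**Working it through.** **Inputs.** Intervention inclusion 1.3.2017 to 30.11.2017, end of data collection 31.12.2017 and last control inclusion 30.11.2016 (section 6.1). Call at least 30 days after surgery (5.1, 9.1.1). Registry contact at 3 months (5.2, 9.1.2). 580 patients per arm and an SSI rate of 20% (10.2). Assumption: uniform accrual.

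**1. Reproducing the stated date.** 30.11.2017 + 30 days = 30.12.2017, a Saturday. The stated end, Sunday 31.12.2017, is day 31. The date therefore follows from the last inclusion plus a bare 30-day follow-up.

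**2. Registry contact.**
- An operation on 30.9.2017 has its 3-month date on 30.12.2017, before the end. An operation on 1.10.2017 has it on 1.1.2018, after the end. Everything from 1.10.2017 onward is affected.
- Calendar days affected: 31 + 30 = 61. Calendar days in the intervention period: 275. 61/275 = 22.2%.
- Weekdays only, since the study operates Monday to Friday (public holidays not removed): 44/197 = 22.3%.
- Patients: 580 × 61/275 = 129. With 540 patients (9/12 of the 720 laparotomies a year in section 10.2): 540 × 61/275 = 120.
- Last patient: 30.11.2017 + 3 months = 28.02.2018, which is 31 + 28 = 59 days after the stated end.

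**3. The same check in the control period.** 30.11.2016 + 3 months = 28.02.2017. Every control patient's 3-month date precedes 31.12.2017, so this cut-off truncates none of them.

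**4. Time left for the telephone procedure.** Count the weekdays of operation for which 31.12.2017 is at most w days after day 30, and scale by 580/197:

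| Days left after day 30 | Operations from | Weekdays | Patients of 580 |
|---|---|---|---|
| at most 1 | 30.11.2017 | 1 | 3 (0.5%) |
| at most 7 | 24.11.2017 | 5 | 15 (2.5%) |
| at most 14 | 17.11.2017 | 10 | 29 (5.1%) |

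**5. Possible size for SSI (illustration).** The documents give no miss rate. Assume a true rate of 20%, about 42 late patients (deliberately more than the 29 above), and a fraction m of their SSIs missed and wrongly counted as no event. The fall in the observed intervention rate is 0.20 × m × 42/580.
- m = 5%: 0.20 × 0.05 × 42/580 = 0.07 percentage points.
- m = 20%: 0.20 × 0.20 × 42/580 = 0.29 percentage points.

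The target difference is 20% − 14% = 6 points.

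**The case against.** The strongest reply is that this is a one-line date problem from which little follows about the results. Four stronger readings are tempting, and the text supports none of them.

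- **Events will be under-ascertained.** The protocol nowhere says that pending calls or registry contacts are dropped on 31.12.2017. SSI surveillance is a hospital routine run by the infectious diseases department under Swissnoso and may simply continue. What the text creates is a risk.
- **The 22% applies to the primary outcome.** The registry contact appears only under mortality, a secondary outcome, and supplements hospital information, the call, the attempts and practitioner contact. A civil registry cannot detect SSI, dehiscence or graded complications. For SSI only the short contact window counts.
- **Level and slope are biased in favour of the closure team.** Patients who cannot be reached are documented as lost, not counted as event-free. Losing them costs precision at the end of the series; the direction of any bias does not follow.
- **Only the intervention arm is affected.** Step 3 shows that time was available for the control contacts, not that they were made. No closing date for control follow-up is given, and the StOP? procedures are not in the protocol.

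The synopsis date should not be read as a plan without follow-up either. The same synopsis promises 30 days, and its bracketed dates are the inclusion periods, so it looks like a mislabelled last-inclusion date.

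All of this narrows the consequence. It does not reconcile the dates: section 6.1 and sections 5.2 and 9.1.2 still cannot both be followed for the October and November 2017 operations.

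**Conclusion.** The point holds as an internal contradiction with a limited consequence. The stated end of data collection precedes the planned registry contact for 22% of the intervention period, about 129 of 580 patients under uniform accrual. It also leaves the last patients one weekend day after day 30 for the whole contact procedure, and about 29 of 580 at most 14 days. If the cut-off is observed, ascertainment may differ between periods, mainly for 30-day mortality. For SSI the likely effect is small: 0.07 to 0.29 percentage points under the assumed miss rates, against a target of 6. The dates are certain. The asymmetry between periods is inferred from the calendar and depends on the control contacts having been completed, which the protocol does not show.

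**What to change.** In section 6.1, move the end of data collection to no earlier than 28.02.2018, plus a short margin for outstanding contacts. Correct the Last-Participant-Out entry in the synopsis to match. State that the same call, practitioner and registry procedure is completed for every patient in both periods, give the date by which control follow-up was closed, and confirm that only events up to day 30 count, whenever the contact takes place. The 30-day horizon is already in the outcome definitions, so that last part only makes the existing rule explicit.

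The cost is a change of protocol wording and a database lock two to three months later. No extra patients and no change of design are needed.

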## Methods of minimising bias

### Randomisation

This study will not be randomized.

### Other methods of minimising bias

In this study all patients within two periods will be included thereby limiting selection bias. However, it is to be expected that the incidence of surgical site infection may decrease over time in response to other measures. Such gradual decrease is expected of occur in both periods and may be corrected.

# STUDY POPULATION

## Eligibility criteria

Participants fulfilling all of the following inclusion criteria are eligible for the study:

- General Consent as documented by signature (Appendix B)
- Patients undergoing elective or emergency laparotomy from Monday to Friday with wound closure from 8:00 until 17:30 and duration of operation.
- Age over 18 years
- Any indication for laparotomy

The presence of any one of the following exclusion criteria will lead to exclusion of the participant:

- Patients < 18 years of age
- Patients with preexisting SSI

## Recruitment and screening

All patients with documented general consent undergoing elective or emergency laparotomy will be included in this study.

## Assignment to study groups

The patients will be assigned to the study groups according to the time point of inclusion. In the period between 1.3.2016 to 30.11.2016 the control group was assessed. Patients operated between 1.3.2017 and 30.11.2017 represent the intervention group.

## Criteria for withdrawal / discontinuation of participants

Not applicable.

# STUDY INTERVENTION

## Identity of Intervention

### Experimental Intervention

The intervention consists of the exchange of the primary surgical team with a second surgical team that consists of one surgeon and one student. The first surgical team then may leave the operation theatre but is continuously accessible for questions.

### Control Intervention

In the control group the abdomen is closed according the clinical routine by the primary surgical team.

The closure in both groups will be identical and consists of a running PDS suture and skin closure according to the surgeons preference.

## Compliance with study intervention

Questionnaires will be filled out by the circulating nurse in the operating theatre in order to identify if the exchange of the surgical team has been performed and what team members were exchanged.

## Data Collection and Follow-up for withdrawn participants

Information of patients that withdraw the general consent will be stored anonymously.

## Trial specific preventive measures

Not applicable.

## Concomitant Interventions (treatments)

The study intervention does not interfere with the medical treatment. Therefore concomitant interventions for other studies may be performed.

# STUDY ASSESSMENTS

## Assessments of outcomes

### Assessment of primary outcome

Surgical site infections (SSI) that occur after surgery will be assessed according to the criteria developed by the Centers for Disease Control and Prevention. Infections will be categorized as incisional (superficial or deep) infections or organ–space infections. Superficial SSI (type 1) involve only skin and subcutaneous tissue and exclude stitch abscesses. Deep SSI (type 2) involve deeper soft tissues, like fascia and muscle, at the site of incision. Organ–space SSI (type 3) involves any organ or space.

Incidence of SSI is assessed according to the clinical routine, following the established protocol of Swissnoso. Data collection according to the Swissnoso protocol will be extended to all surgeries included. The protocol includes direct contact to the patient:

- All patients receive a standardised follow-up phone call at least 30 days after the operation to assess incidence of SSIs and other complications.
- If patients do not respond to follow-up phone calls, five documented attempts to contact the patients followed by rapid contacts with the subject’s general practitioner or other medical staff involved in the medical treatment of the patients, will be performed before loss of follow-up is documented.

### Assessment of secondary outcomes

Postoperative mortality

The assessment of postoperative mortality will be included into the telephone interview and assessed as follows:

Mortality at 30 days: Observer receives the information from the postoperative stay that the patient died

Complications: Assessment according to Clavien-Dindo Grading

Postoperative fascial dehiscence at 30 days postoperative: As reported in prior reports / operation reports.

Observer receives the information during the follow-up phone call that the patient died. If patients do not respond to follow-up phone calls, five documented attempts to contact the patients followed by rapid contacts with the subject’s general practitioner or other medical staff involved in the medical treatment of the patients, will be performed before loss of follow-up is documented. In addition, the Zivilstandsamt will be contacted once 3 months after surgery.

### Assessment of other outcomes of interest

In order to perform subgroup analyses or adjusted analyses, following variables are assessed:

- Type of operation (primary, secondary surgery)
- Grade of contamination
- Duration of the procedure
- Height and weight of the patient
- Comorbidities

### Assessment of safety outcomes

As the standard treatment will not change in this study, any deviation from the standard treatment that may be related to the intervention will be recorded.

# STATISTICAL METHODS

## Hypothesis

Null Hypothesis: The introduction of a trained closure team does not change the incidence of SSI after abdominal surgery

Alternative Hypotheses: The introduction of a trained closure team changes the incidence of SSI after abdominal surgery.

## Determination of Sample Size

Sample size: The incidence of SSI after abdominal surgery in the department for Visceral Surgery and Medicine is 20%. The aim is to detect a reduction of the overall incidence rate of SSI from 20% to 14% after a follow-up of 30 days. We defined the level of significance at 5% and power of 80%, assuming normal approximation to binomial distribution requires 484 surgeries in each cell, thus 968 patients overall. In the ongoing StOP?-study we have a drop out and study refusal rate of maximal 20%. Thus, a total of 1160 participants (580 per arm) need to be included.

Duration: The average number of laparotomies from 8:00 AM to 5:30 PM from Monday to Friday per year are 720. The study schedule includes first 9 months in the control (baseline: 2^nd^ arm of the STOP? Study) and then 9 months in the intervention group.

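### Section 6.1 aims for 1785 participants against 1160 elsewhere, and 580 per arm falls short of the required 484 evaluable if loss reaches the stated maximum of 20%

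*Protocol*

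**What the plan says.** Section 10.2 (Determination of Sample Size) sets the target effect: "The aim is to detect a reduction of the overall incidence rate of SSI from 20% to 14% after a follow-up of 30 days". It fixes significance at 5% and power at 80%, without saying whether the test is one-sided or two-sided, and states the need as "assuming normal approximation to binomial distribution requires 484 surgeries in each cell, thus 968 patients overall". It then allows for loss: "In the ongoing StOP?-study we have a drop out and study refusal rate of maximal 20" per cent. From this it concludes: "Thus, a total of 1160 participants (580 per arm) need to be included".

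The English synopsis repeats these figures. The German synopsis also goes from 484 to 580 per arm and 1160 overall, but treats the 20% as the expected dropout rate, not as a maximum.

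Section 6.1 (General study design) gives another total, with no derivation: "We aim to include a total of 1785 participants".

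The alternative hypothesis in Section 10.1 has no direction: "The introduction of a trained closure team changes the incidence of SSI after abdominal surgery".

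**The concern.** Two things are wrong in the enrolment figures. First, the design section and the sample-size section give totals that cannot both be the target, so an ethics committee, monitor or reader cannot tell which one the protocol commits to. Second, the step from 484 to 580 adds 20% of the evaluable number, whereas a loss rate acts on the number included. At the loss the protocol names, the stated inclusion number therefore misses the stated evaluable number. Power is also at stake. The 80% is quoted for a number that the plan does not secure at its own loss rate, and that number rests on a test direction which the hypothesis section does not support.

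**Working it through.** **Inputs.** Control rate p1 = 0.20, intervention rate p2 = 0.14, alpha 5%, power 80%, 484 evaluable per arm, loss at most 20%, 580 per arm and 1160 in total (all Section 10.2); 1785 in total (Section 6.1); non-directional alternative (Section 10.1).

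**1. Reproduce 484.** The normal approximation with pooled variance under the null, without continuity correction, is

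n = [z_alpha x sqrt(2 x pbar x (1 - pbar)) + z_power x sqrt(p1(1 - p1) + p2(1 - p2))]^2 / (p1 - p2)^2, with pbar = 0.17.

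The two roots are sqrt(0.2822) = 0.5312 and sqrt(0.2804) = 0.5295; z_power = 0.8416.

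- One-sided 5% (z = 1.645): (0.8738 + 0.4457)^2 / 0.0036 = 483.6, so **484**. This matches the protocol.
- Two-sided 5% (z = 1.960): (1.0412 + 0.4457)^2 / 0.0036 = 614.1, so **615**. With continuity correction it is 647.

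Unpooled and arcsine variants give about 481 to 482 one-sided and 611 two-sided. Only a one-sided test yields 484.

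**2. Reproduce 580 and 1160.** 484 x 1.2 = 580.8 and 968 x 1.2 = 1161.6, the evident source of 580 and 1160.

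**3. Apply the loss to the number included.**

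- 580 x 0.8 = **464** per arm, 928 in total: 20 per arm and 40 in total below the stated need.
- To keep 484: 484 / 0.8 = 605 per arm, 1210 in total.
- Loss at which 580 still keeps 484: 1 - 484/580 = 16.6%.

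**4. Power of the two-proportion comparison, 20% against 14%.** Power = Phi[(0.06 x sqrt(n) - z_alpha x 0.5312) / 0.5295].

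| Evaluable per arm | One-sided 5% | Two-sided 5% |
|---|---|---|
| 464 | 78.5% | 68.2% |
| 484 | 80.0% | 70.1% |
| 580 (no loss) | 86.0% | 77.7% |

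**5. Compare the totals.** 1785 - 1160 = 625, and 1785/1160 = 1.54. An odd total cannot be two equal arms. The stated inputs lead to 1160 or 1210, or, two-sided with 20% loss, to 615/0.8 = 769 per arm and 1538 in total. None is 1785.

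**6. Check what the recruitment windows allow.** Section 10.2 gives 720 laparotomies a year in the eligible hours. Assuming even accrual, nine months give 720 x 9/12 = 540, below both 580 and 605.

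**The case against.** The strongest case on the other side has four parts.

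- **The slip is small.** On the basis that yields 484 it costs about 1.5 points of power. This stands.
- **464 is not certain.** A reader might infer that 580 will in fact leave 464. The documents do not support that: Section 10.2 calls 20% a maximum and includes refusals in it. Signed general consent is an inclusion criterion (Section 7.1), so those who refuse it may never count among the 580. The rate is not split, so loss after inclusion could be lower. On the other side, the German synopsis calls 20% the expected dropout and derives the number to be included from it. What stands is that 464 is the worst case under Section 10.2; the inflation step is wrong either way.
- **The calendar, not the target, governs recruitment.** Assignment is by fixed dates (Section 7.3), all patients in both periods are to be included (Section 6.2), and no rule stops at 580. This stands. It limits the practical harm but does not reconcile 1160 with 1785.
- **The power figures are not those of the planned analysis.** Section 10.4.1 plans a covariate-adjusted interrupted time series. This stands too: the figures above describe the simple comparison on which Section 10.2 bases its number, and nothing more.

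**Conclusion.** The enrolment figures are wrong as written. The contradiction between 1785 and 1160 needs no assumption. The inflation error follows from the protocol's own 484 and 20%: 580 secures 484 only if loss is at most 16.6%, and at the stated maximum 464 per arm remain.

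Two stronger readings are tempting and do not hold. The first is that the inflation error brings power down to 68%. Most of that fall comes from sidedness: with a two-sided test, power is already 70.1% at 484, about 10 points below 80%, and going from 484 to 464 takes about 2 points more. The second is that 605 per arm and 1210 in total are simply the right figures. They repair the dropout step only. After a 20% loss, 605 returns to 484 and so to about 70% two-sided power. They also cannot be met by rewording: the control period ended on 30.11.2016, before the protocol date of 18.01.2017, and the protocol's own volume gives about 540 per period.

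The power figures assume independent patients, true rates of 20% and 14%, equal arms and a simple two-proportion test. The 540 assumes even accrual over the year.

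**What to change.** Keep the fixed recruitment windows and make these text changes:

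1. In Section 6.1, replace 1785 by the total used in Section 10.2 and the synopses.
2. In Section 10.2 and both synopses, state that 580 per arm leaves 464 evaluable if loss reaches 20%. Describe the 20% in the same way in both languages, as either a maximum or an expected rate.
3. Declare whether the test is one-sided or two-sided, consistently with Section 10.1, and give the power that follows at 464: 78.5% one-sided or 68.2% two-sided for the simple comparison. If the test is two-sided, the 80% claim has to be withdrawn for this sample size.

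Do not substitute 605 and 1210 on their own. A larger target would need the sidedness settled first (a two-sided test with 20% loss needs 769 per arm, 1538 in total) and different recruitment windows.

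The cost is protocol wording and restated figures in four places: Sections 6.1 and 10.2 and the two synopses. Recruitment, follow-up and data collection do not change.
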